### Secondary Measures

The following measures will also be collected: socio-demographic data including age, gender, education, race, occupation, family income; type of health coverage and degree of health service utilization; history and current status of tobacco, biomass fuel or occupational exposures; level of alcohol consumption; physical activity including type, frequency and intensity; nutritional intake; self-reported past medical history; pharmacologic and non-pharmacologic treatment received for prior medical history; self-reported family history and history of hospital admissions due to pulmonary disease during childhood. Blood pressure and anthropometrics, including height, weight, abdominal and hip circumference, will also be measured. Biochemical measurements such as lipid profile, serum creatinine and glucose will be conducted and EKG will be performed.

### Instruments

Information about current and former cigarette smoking, including age at which smoking was initiated, years of smoking, amount of cigarettes smoked per day, cessation attempts and treatments will be assessed by the Global Adult Tobacco Survey (GATS)[15]. Use of other forms of tobacco, exposure to passive cigarette smoking and indoor pollution will also be assessed using other questionnaires to assess indoor heating and cooking using biomass fuels. Nutritional information will be collected using a semi-quantitative food frequency questionnaire (FFQ) adapted from the National Cancer Institute validated by our research team to be used in Argentina, Chile and Uruguay[16]. Depression and anxiety will be assessed by the nine item Patient Health Questionnaire (PHQ-9)[17], which has been validated in Argentina[18]. Traumatic, stressful events and spirituality will be assessed through the Hispanic Community Health Study/Study of Latinos (HCHS/SOL) study questionnaire which has been cross-culturally adapted[19]. The International Physical Activity Questionnaire (IPAQ)[20] will be used to assess physical activity. SF-12[21] and European Quality of Life 5-Dimensions (EQ5D)[22] questionnaires will be used to evaluate health-related quality of life and social preferences, respectively through locally validated versions of these tools[23,24]. The remainder of the questionnaires used to gather participant information have been cross-culturally adapted from the HCHS/SOL [19].

Spirometric measurements will be performed with identical, portable, battery operated, ultrasound transit-time based EasyOne^™ ^spirometers (Medical Technologies, Chelmsford, Massachusetts and Zürich, Switzerland). Calibration will be checked daily with a three-liter syringe. Test results will be stored in the spirometer memory and downloaded weekly to a central computer. Trained professionals will first administer a questionnaire to determine patient eligibility, as described above. Trained personnel will then perform spirometry following ATS guidelines. Spirometry will be conducted with subjects in the seated position, wearing a nose clip and using a disposable mouthpiece. Subjects will perform up to eight forced expiratory maneuvers with forced vital capacity (FVC) and forced expiratory volume in the first second (FEV1) reproducible within 150 ml. A beta-agonist bronchodilator, Albuterol 200 ug, will be administered and repeat spirometry will be performed 15 minutes later, using the same criteria. All field methods have been tested in pilot studies at each site.

All health care professionals involved in the study have participated in a two-day spirometry and questionnaire training led by the main study coordinator, a pulmonologist from the coordinating center ([name]). The spirometry course focused on the acceptability and reproducibility of a pulmonary function test and the factors associated with an unacceptable spirometry test. The technicians were certified if they were able to perform 10 pulmonary function tests that met the 2005 ATS/ERS criteria.

## Statistical Analysis

### Sample size

The calculated sample size is 6,000 participants (1,500 per site). This sample will be sufficient to provide precise estimates of the prevalence of COPD by gender and site and associated risk factors, in three age-defined categories: 45 to 54, 55 to 64 and 65 to 75 years old. The proposed sample size is sufficient to comply with the precision requirements of a complex sample that assumes a design effect of 1.5 and the prevalence of risk factors of interest of 5% or greater (Table 2). All power calculations used a statistically significant alpha level of 0.05 and a statistical power of 85%, which will permit detection of moderate and large relative risks.

**Table 2 T2:** Sample size for a highly complex study design for effect and design of specific proportion

Proportion	Design Effect				
	1.0	1.5	2.0	2.5	3.0

0.26-0.50	30	45	60	75	90

0.25	32	48	64	80	96

0.20	40	60	80	100	120

0.15	53	80	107	133	160

0.10	80	120	160	200	240

0.05	160	240	320	400	480

### Statistical Analysis

General characteristics of the population will be described. For continuous variables, mean and median, range, standard deviation, and/or quartile range will be calculated according to the distribution of each variable. In the case of categorical variables, absolute and relative frequencies will be calculated.

In order to determine the prevalence and incidence of COPD and patient characteristics and risk factors, the design effect of the first stage unit of sampling will be considered. Weighting will be based on the relation between the number of individuals included in the study and the population size and composition of each site according to the most recent census data. Likewise, the analysis will be carried out by socioeconomic strata, gender and age categories.

To assess the association between risk factors and COPD, linear regression and simple and multiple logistical regressions will be used according to the nature of the response variables. Continuous variables that are not normally distributed will be evaluated by the application of transformations and categorizations wherever applicable[25]. The secular trends in risk factors over time will be evaluated with methods of statistical analysis that take into account the correlation between repeated measures. To evaluate the changes in risk factors over time by sub-groups of interest, generalized estimation equations will be used. To estimate the rate of accumulated COPD incidents, the Kaplan-Meir method will be used. The log rank test will be used to compare the differences between the curves of accumulated incidence events. The log rank test of trend will be applied to analyze the relationship between the accumulated risk by quartile group or by created groups of interest. In order to quantify the relationship between risk factors and the incidence of COPD, the Cox Proportional Hazards method will be used. Potential confounders and interactions will be explored.

Appropriate diagnostics will be carried out to test goodness of fit, co-linearity, and atypical observations in each model. In all cases, fulfillment of assumptions in the model by means of exploration of residual behavior will be verified. Statistical analysis software STATA 10.0 and SAS 9.0 will be used[26,27].

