### Sampling Procedure

A randomized, three-staged, stratified, cluster sampling strategy was usedin order to select a representative sample of the general population aged 45 to 75 years of age. The first stage selected 60 census enumeration areas using probability proportional to size, with implicit stratification by socioeconomic level of the enumeration area. The second stage selected 40 households from each enumeration area using systematic sampling. The third stage selected one household member between 45-75 years of age for the study. The final sampling was stratified by gender, with 50% men and 50% women, and age distribution based on recent population census data[13,14](Figure 1).

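### The stated census-based weights contain no factor for drawing one member per household, so the prevalence estimate can be biased if that member was drawn at random

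*Protocol article*

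**What the plan says.** The Sampling Procedure section of the protocol article describes three stages:

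- Areas: "The first stage selected 60 census enumeration areas using probability proportional to size".
- Households: "The second stage selected 40 households from each enumeration area using systematic sampling".
- Persons: "The third stage selected one household member between 45-75 years of age for the study". The article does not say how that member was picked.

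It then adds: "The final sampling was stratified by gender, with 50% men and 50% women, and age distribution based on recent population census data".

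The Statistical Analysis section gives the weighting rule: "Weighting will be based on the relation between the number of individuals included in the study and the population size". The sentence does not end there; the census side of the ratio is "the population size and composition of each site according to the most recent census data". For the design, "the design effect of the first stage unit of sampling will be considered", and "the analysis will be carried out by socioeconomic strata, gender and age categories". Neither section brings the number of eligible residents in a household, or a within-household selection probability, into the weight.

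**The concern.** Drawing one person per household normally makes a person's chance of selection depend on how many eligible people live there. Under a random draw, someone aged 45 to 75 who lives with one other eligible person has half the chance of someone who is the only eligible resident. A weight formed from sample counts against census counts restores the margins it is built on (site, sex, age). It cannot restore household size, which varies inside each age-sex cell.

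At stake is the phase-one primary outcome, COPD prevalence in a sample meant to represent the general population aged 45 to 75. Several exposures of interest, such as indoor biomass smoke, passive smoking and family income, belong to the household. A link between household composition and COPD is therefore plausible, though no figure in the article shows one.

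**Working it through.** **1. The plan's own figures.** The article states no weight and no expected prevalence, so there is no stated bias to reproduce. Its sample size does reproduce. The Table 2 entries for proportions 0.05 to 0.25 follow n = 8 × design effect / proportion (a rule inferred from the table). At a design effect of 1.5 and a proportion of 0.05, n = 8 × 1.5 / 0.05 = 240. Four sites × two sexes × three age groups give 24 cells, and 6,000 / 24 = 250 per cell. I use the design effect of 1.5 below.

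**2. Which stage leaves unequal chances.** If the size measure for the areas is the household count (not stated), a household's chance is 60 × (N_a/N) × (40/N_a) = 2,400/N, where N_a is the number of households in the area and N the total. This is the same for every household. The person stage then multiplies it by 1/k when one of k eligible residents is drawn at random, and 1/k is the term that the stated weight lacks.

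**3. Size of the distortion.** Assumptions: households hold one or two eligible people; h is the share of households with two; R is the prevalence ratio, within an age-sex cell, of one-eligible to two-eligible households; P is the true prevalence.

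- Population share of people in two-eligible households: T = 2h / (1 + h). Their sample share is h.
- p2 = P / [(1 - T)R + T] and p1 = R × p2.
- Expected estimate = (1 - h)p1 + h × p2. Bias = estimate - P.

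For h from 0.3 to 0.6, people who are the only eligible resident form 70% to 40% of the sample but 54% to 25% of the population. Example with h = 0.5, R = 1.5, P = 19.7%: T = 0.667, p2 = 16.9%, p1 = 25.3%, estimate 21.1%, bias +1.41 points.

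P of 8% and 19.7% approximates the range of city prevalences that the Background cites (7.8% to 19.7%); 15% lies between. Half-width = 1.96 × √(1.5 × P(1 - P)/n).

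| P | R = 0.8 | R = 1.0 | R = 1.2 | R = 1.5 | Half-width, n = 6,000 | Half-width, n = 1,500 |
|---|---|---|---|---|---|---|
| 8% | -0.25 to -0.30 | 0 | +0.23 to +0.25 | +0.51 to +0.57 | 0.84 | 1.68 |
| 15% | -0.47 to -0.56 | 0 | +0.43 to +0.47 | +0.95 to +1.07 | 1.11 | 2.21 |
| 19.7% | -0.62 to -0.74 | 0 | +0.56 to +0.62 | +1.25 to +1.41 | 1.23 | 2.47 |

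All biases and half-widths are in percentage points. The bias does not shrink as n grows, so it weighs most on the pooled estimate.

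**4. Dependence on how the member was picked.** Assume 20% of households hold a lone man, 30% a lone woman and 50% a couple, with prevalence 18% (lone) against 12% (couple) in men and 12% against 8% in women.

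- Truth: men (0.2 × 18 + 0.5 × 12)/0.7 = 13.7%; women (0.3 × 12 + 0.5 × 8)/0.8 = 9.5%; with men 0.7/1.5 of the population, 11.5% overall.
- Random member, weighted by sex: men (0.2 × 18 + 0.25 × 12)/0.45 = 14.7%; women (0.3 × 12 + 0.25 × 8)/0.55 = 10.2%; overall 12.3%.
- Each household pre-assigned a sex, weighted by sex: living with a spouse no longer changes a person's chance, and the result is 11.5%, with no bias.

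**5. Cost of including the factor.** The Kish design effect for weights 1 and 2 is [(1 - h) + 4h] / (1 + h)². This is 1.9/1.69 = 1.12 at h = 0.3 and 2.8/2.56 = 1.09 at h = 0.6.

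**The case against.** The strongest reply has four parts.

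- **This is a condensed article.** A fuller plan may define the weights, and a rule stated as what the weights rest on does not exclude a base weight. That stands as a caution. Still, the article chose to state the basis, and that basis leaves out a term which its own sampling design may require.
- **The selection chance is not known to be 1/k.** This stands. The article mentions stratification by sex and age but no mechanism, and under sex pre-assignment the problem can vanish (step 4).
- **Bias needs an association.** This stands too. Without a link between COPD and household composition inside age-sex cells the bias is zero, and its sign is open.
- **In the planned subgroups the effect is small against sampling error.** In a cell of 250 at 10% prevalence, the half-width is 4.6 points. The concern is mainly for site and pooled estimates.

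A reader might also infer that the weights merely scale to totals and so leave the 50/50 sex split uncorrected. The text does not support that: weighting to census composition, read with the sex and age strata, plausibly corrects it. Nor does the text show that the intervals omit the variance from unequal weights. The plan names both weights and a first-stage design effect, and standard weighted variance estimation on first-stage clusters reflects unequal weights.

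**Conclusion.** The point holds in conditional form. Applied as written, census-composition weights cannot correct unequal within-household chances. If the member was drawn at random, the primary prevalence estimate can be off by about -0.7 to +1.4 points over the assumed range (h from 0.3 to 0.6, R from 0.8 to 1.5, P from 8% to 19.7%). At P = 15% the range is -0.56 to +1.07 points, against half-widths of about 1.1 points pooled and 2.2 points per site. The household mixes and prevalence ratios are my assumptions, not figures from the article.

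A stronger reading would be that the estimate is certainly biased towards people who are the only eligible resident, with badly failing intervals. For instance, if such people are 40% of the population and prevalence is 15% against 10%, the estimate is 12.9% for a true 12.0%, and 95% coverage is about 87% per site and 62% pooled. That arithmetic is sound but sits on the upper side. With 12% against 10%, coverage is about 94% per site and 89% pooled. The documents establish neither the random draw nor the association, so they do not support bias as a fact.

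**What to change.** State how the household member was chosen. Define the base weight as the inverse of the selection probability across the three stages: area, household within area, and member within household. The last term uses the number of eligible residents aged 45 to 75, counted within the selected sex if selection was sex-specific. Then calibrate to census site-by-age-by-sex totals, and use this weight for the prevalence estimates with the enumeration area as the cluster.

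The change is to the analysis wording, but it needs the count of eligible residents for each sampled household. The article does not say that this count was recorded, so its availability should be confirmed.

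The statistical price is a weighting design effect of about 1.1, which widens intervals by about 5% (√1.1 = 1.05). If the planned 1.5 does not already include weighting, the combined value is 1.5 × 1.1 = 1.65. The Table 2 rule then asks for 8 × 1.65 / 0.05 = 264 per cell at a 5% proportion, against 250 available. With 250 per cell, the smallest proportion that meets the rule is 8 × 1.65 / 250 = 5.3%, a minor loss.

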**Methods/Design:**

PRISA is an observational, prospective cohort study with at least four years of follow-up. In the first year, PRISA has employed a randomized three-staged stratified cluster sampling strategy to identify 6,000 subjects from Marcos Paz and Bariloche, Argentina, Temuco, Chile, and Canelones, Uruguay. Information, such as comorbidities, socioeconomic status and tobacco and biomass exposure, will be collected and spirometry, anthropometric measurements, blood sampling and electrocardiogram will be performed. In year four, subjects will have repeat measurements taken.

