## Methods/Design

The PRISA study is an observational, prospective cohort study with at least 4 years of follow-up. Subjects 45-75 years of age are being recruited using a multistage cluster sampling method. The study is composed of two phases. In the first phase, baseline data will be collected regarding exposure to risk factors and prevalence of COPD. In the second phase, annual follow-up data will be obtained to determine the rate of incident COPD, the association between exposure and development of COPD, and the rate of decline in lung function exhibited by COPD subjects identified in the first phase. Inclusion criteria were men and women aged 45-75 years of age, permanent resident at one of the study locations for at least six months each year and willingness to offer written consent. Exclusion criteria were an expressed intenton to relocate within the next four years, inability to respond to the questionnaire due to cognitive impairment or language difficulty, active tuberculosis, pregnancy, or history of detached retina and cardiac infarction or ocular, thoracic or abdominal surgery within prior six weeks (contraindications to spirometry testing). A total of 6,000 non-institutionalized, mainly urban, (1,500 participants per site), men and women will be recruited from Bariloche and Marcos Paz, Argentina, Temuco, Chile, and Canelones, Uruguay.

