### Primary Outcome

The primary outcome for phase one of the study is the prevalence of COPD, as defined by the Global initiative for Obstructive Lung Disease (GOLD). The lower limit of normal (LLN) values for these populations will be calculated, using the American Thoracic Society (ATS) and European Respiratory Society (ERS) guidelines. The primary outcome for the four-year follow-up is the change in lung function. Secondarily, the incidence of COPD will be calculated. These criteria are listed in Table 1.

**Table 1 T1:** Spirometric criteria for the definition of COPD

Spirometry Criteria	Definition
GOLD[1]	Post-bronchodilator forced expiratory volume in the first second (FEV1)/forced vital capacity (FVC) < 70 and FEV1 < 80% of predicted value
ATS[28,29]	Post-bronchodilator FEV1/FVC below the LLN and FEV1 < 100% of predicted value
ERS[30]	Post-bronchodilator FEV1/FVC < 88% of the predicted value for men and < 89% for women

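### The article does not settle whether spirometry is repeated annually or only in year four; if only in year four, Kaplan-Meier, log-rank and Cox do not fit the COPD incidence data

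*Protocol article*

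**What the plan says.** - **Outcome.** Primary Outcome makes change in lung function the main follow-up outcome and adds: "Secondarily, the incidence of COPD will be calculated". All three definitions in Table 1 are post-bronchodilator spirometric criteria. The GOLD row, for example, reads "Post-bronchodilator forced expiratory volume in the first second (FEV1)/forced vital capacity (FVC) < 70 and FEV1 < 80% of predicted value".
- **Schedule.** Methods/Design describes the cohort thus: "The PRISA study is an observational, prospective cohort study with at least 4 years of follow-up". The Methods/Design part of the Abstract says: "In year four, subjects will have repeat measurements taken". The main Methods/Design section says of the second phase that "annual follow-up data will be obtained to determine the rate of incident COPD", without saying what is collected each year.
- **Analysis.** Under Statistical Analysis: "To estimate the rate of accumulated COPD incidents, the Kaplan-Meir method will be used". Then: "The log rank test will be used to compare the differences between the curves of accumulated incidence events". A log-rank trend test follows, and for risk factors: "In order to quantify the relationship between risk factors and the incidence of COPD, the Cox Proportional Hazards method will be used". The section does not mention interval censoring.

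**The concern.** Kaplan-Meier, log-rank and Cox methods assume that an event time is observed, or at least that follow-up ends at a time unrelated to whether the event has occurred. COPD as defined in Table 1 is found only when someone is tested. With one repeat test, all that is known is whether onset came before or after that visit. If the visit date is entered as the time, cases and non-cases alike leave the risk set on their appointment day, and the curve describes the appointment calendar.

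Incidence and its risk factors are stated aims, meant to inform public health policy. A curve with the wrong level and shape, or a hazard ratio that depends on who was seen first, would mislead on both. How much this matters depends on the retest schedule, which the article leaves open.

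**Working it through.** **1. The passages side by side.** A case needs spirometry (Table 1). The only repeat measurement with an explicit date is in year four (Abstract). Methods/Design has annual data serving incidence. Either the annual data include spirometry, and the Abstract is incomplete, or they do not, and they cannot classify a case under Table 1. The text does not decide between these.

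**2. Inputs.** The article gives no expected incidence, hazard ratio or visit window, so there is no stated figure to reproduce. Assumed: 4,300 people at risk, 30% exposed, true hazard ratio 2.0, four-year risk 5% in the unexposed, exponential onset, one visit uniform over years 4 to 5, visit date used as event or censoring time.

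**3. True risk.** Hazard in the unexposed h = -ln(0.95)/4 = 0.01282 per year. Overall risk F(t) = 0.7(1 - e^(-ht)) + 0.3(1 - e^(-2ht)), which is 6.8%, 7.2% and 7.8% at 4.25, 4.5 and 4.9 years.

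**4. What Kaplan-Meier estimates.** With visits uniform on (a, b), people leave the risk set at rate 1/(b - v), and a fraction F(v) of them count as events. With F roughly constant at p, the curve is 1 - ((b - v)/(b - a))^p. Taking p = 0.07:

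| Time (years) | Approximation | Simulation | True |
|---|---|---|---|
| 4.25 | 1 - 0.75^0.07 = 2.0% | 1.9% | 6.8% |
| 4.5 | 1 - 0.50^0.07 = 4.7% | 4.6% | 7.2% |
| 4.9 | 1 - 0.10^0.07 = 14.9% | about 15.6% | 7.8% |

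The curve is too low early in the window and too high late in it.

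**5. What Cox estimates.** At visit date v the ratio is [F1(v)/F0(v)] × [visit rate in exposed / visit rate in unexposed].
- *Timing unrelated to exposure.* The second factor is 1. At 4.5 years the first is 0.1090/0.0561 = 1.94, a risk ratio. Simulated: 1.90 to 1.91, a mild attenuation.
- *Exposed seen three months later* (window 4.25 to 5.25). At v = 4.5 the visit rates are 1/0.75 and 1/0.50, a factor of 0.67, giving 1.94 × 0.67 = 1.3. At v = 4.9 they are 1/0.35 and 1/0.10, a factor of 0.29, giving 0.55. Before 4.25 no exposed person is seen. Simulated overall: 0.75 to 0.77.
- *Exposed seen three months earlier.* Simulated: 4.9.

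**6. A second set of assumptions.** 5,000 at risk, 50% exposed, true hazard ratio 2, four-year risk in the unexposed 3% to 20%:

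| Examination scheme | Kaplan-Meier, unexposed | Cox ratio |
|---|---|---|
| One common examination at year 4 | Single step; correct at year 4 | 1.96 to 2.00 (Efron ties), 1.81 to 1.95 (Breslow ties) |
| One examination, years 3.5 to 4.5 | 6.5% at year 4 for a true 10%; 27.1% at 4.45 years for a true 11.1% | 1.80 to 1.96 |
| Same, exposed 3 months earlier / later | – | 4.7 to 5.1 / 0.73 to 0.80 |
| Annual spirometry | 5.2% at 2 years (true 5.1%); 10.2% at 4 years (true 10%) | 1.96, equal to the ratio from exact onset times in the same data |

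The annual row is for a 10% four-year risk.

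**7. The alternative model.** On the inputs of step 2, a complementary log-log model with log time as offset gave 1.97 to 2.01 under all three timings. With a rising hazard (Weibull shape 2) and the same shifts it gave 2.12 and 1.91.

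**The case against.** **The year-four-only premise is not established.** A reader might infer that COPD can be detected only in year four. The Abstract does not say only, and Methods/Design points to annual data for incidence. This objection stands: the point is conditional on the schedule. Annual spirometry removes nearly all the bias when visit timing is unrelated to exposure. A three-month shift by exposure with annual visits spread by six months either way still moved the ratio to 1.72 or 2.29, but nothing in the article suggests such a shift.

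**The reversed hazard ratio needs exposure-dependent timing.** This also stands. The article gives no sign of it, and without it the Cox ratio is close to the truth. The distortion of the Kaplan-Meier curve does not need it; it needs only varying visit dates used as event times.

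**A full protocol or analysis plan may say how onset is dated.** It may, and the absence of such a rule is not the finding. The finding is that the article names right-censored methods, while the only dated repeat it gives cannot supply event times. Setting every time to exactly four years removes most of the bias, but Kaplan-Meier then becomes a simple proportion.

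**Clustering.** A reader might also infer that the log-rank test ignores the sample design. The Statistical Analysis section says that the first-stage design effect will be considered when incidence is determined, and it specifies weighting. No finding on inflated type I error is supported.

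**The alternative was tested on favourable data.** In part: exponential onset matches the offset model exactly. Under a rising hazard its error was small but not zero.

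**Conclusion.** The point holds conditionally, at moderate severity. The Abstract and Methods/Design do not agree on when spirometry is repeated, and must be reconciled.

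- **Year four only, with dates spread over a window and used as event times:** the Kaplan-Meier curve is badly wrong, at about a quarter of the true risk early in the window (1.9% against 6.8%) and twice it late (15.6% against 7.8%). The Cox ratio is mildly attenuated, at about 1.9 for a true 2.0, unless timing differs by risk factor. A three-month difference then gave about 0.76 or 4.9.
- **Year four only, at a common time:** the four-year risk is right and the ratio nearly so.
- **Annual spirometry, timing unrelated to exposure:** the bias is negligible.

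All simulation inputs are assumptions. A reader might infer that the study's main results are at risk. They are not: prevalence and change in lung function do not use these methods, and incidence is secondary.

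**What to change.** 1. State in both the Abstract and Methods/Design when post-bronchodilator spirometry is repeated and what the annual contacts collect.
2. If it is repeated only in year four, replace the three methods for incidence. Report weighted cumulative incidence among participants free of COPD at baseline. Model risk factors with a design-based complementary log-log model, or another interval-censored model, with the log of time between spirometries as offset or covariate. Take group comparisons and trend tests from its Wald tests, with the enumeration area as cluster.
3. If it is annual, the named methods can stay. A discrete-time version with period terms is optional.

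The cost is wording in the article and the analysis plan. Standard software fits the model, and no new data are needed.

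### Kaplan-Meier for accumulated COPD incidence names no provision for death as a competing event; where onset is observed, it modestly overstates the share who develop COPD

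*Protocol article*

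**What the plan says.** The Statistical Analysis section of the protocol article fixes the methods for incident COPD:

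- Estimator: "To estimate the rate of accumulated COPD incidents, the Kaplan-Meir method will be used".
- Comparison of curves: "The log rank test will be used to compare the differences between the curves of accumulated incidence events".
- Trend: "The log rank test of trend will be applied to analyze the relationship between the accumulated risk by quartile group", or by other groups to be created.
- Risk factors: "In order to quantify the relationship between risk factors and the incidence of COPD, the Cox Proportional Hazards method will be used".
- Strata: "Likewise, the analysis will be carried out by socioeconomic strata, gender and age categories".

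No competing-risk estimator is named, and no section says what happens to participants who die without COPD.

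Three other points bear on this. Methods/Design gives an age range of 45-75 and at least four years of follow-up. Primary Outcome makes change in lung function the main follow-up outcome and COPD incidence secondary. On timing, the Abstract places the repeat measurements in year four, while Methods/Design speaks of follow-up data obtained annually without saying whether these include spirometry.

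**The concern.** Accumulated incidence is a statement about how many people develop the disease. In this age range some participants will die first, and they can no longer develop COPD. Kaplan-Meier with COPD as the only event has just two outcomes for a participant, event or censoring, so a death without COPD would ordinarily be censored. The method then treats the dead as if they still carried the same future risk of COPD as the survivors. The result is the risk in a population where nobody dies.

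The article weights to census composition and wants the results to inform public health policy, so the useful quantity is the share of the real population who develop COPD. When onset is observed, the gap between the two quantities grows with mortality. It therefore differs between the age categories that the plan sets side by side. It is systematic, so a larger sample does not remove it.

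**Working it through.** **Inputs.** From the article: four years of follow-up, 6,000 participants (1,500 per site), design effect 1.5. The article gives no COPD incidence and no death rate, so there is no planned figure to reproduce. All hazards below are assumptions, shown over a range. Let h be the annual COPD hazard and m the annual hazard of death without COPD, both constant.

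**Step 1: onset observed, deaths censored.**

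- Kaplan-Meier target: 1 − exp(−4h)
- Cumulative incidence with death competing: h/(h+m) × [1 − exp(−4(h+m))]

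| h | m | 1 − KM | Cumulative incidence | Relative excess | Points |
|---|---|---|---|---|---|
| 0.005 | 0.005 | 1.98% | 1.96% | 1% | 0.02 |
| 0.01 | 0.01 | 3.92% | 3.84% | 2% | 0.08 |
| 0.02 | 0.02 | 7.69% | 7.39% | 4% | 0.30 |
| 0.02 | 0.03 | 7.69% | 7.25% | 6% | 0.44 |
| 0.03 | 0.05 | 11.31% | 10.27% | 10% | 1.04 |

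The relative excess is about 2m, which is half the four-year death hazard.

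**Step 2: effect on a contrast between groups.** Compare h = 0.02, m = 0.03 with h = 0.01, m = 0.01. The four-year risk ratio is 1.96 by Kaplan-Meier and 1.89 by cumulative incidence. The risk difference is 3.77 against 3.41 points.

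**Step 3: size against precision.** The 95% half-width is 1.96 × √[1.5 × p(1−p)/n]. At p = 7.7% it is 4.05 points for n = 250 (6,000 divided by 4 sites × 2 sexes × 3 age categories), 1.65 for n = 1,500 and 0.83 for n = 6,000. These are lower bounds on the width, because participants with COPD at baseline are not at risk of incident COPD.

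**Step 4: spirometry at baseline and year four only.** COPD can now be detected only in those alive at year four. Let mortality after onset be k × m.

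- P1 (alive with COPD) = ∫ h exp(−(h+m)t) exp(−km(4−t)) dt, for t from 0 to 4
- P0 (alive without COPD) = exp(−4(h+m))
- Kaplan-Meier at year four = P1/(P1+P0), the COPD share among survivors
- An estimate that counts every earlier death as COPD-free = P1

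With h = m = 0.02, the true cumulative incidence is 7.39%:

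| k | Kaplan-Meier | Error | All deaths counted COPD-free | Error |
|---|---|---|---|---|
| 1 | 7.69% | +4.0% | 7.10% | −4% |
| 2 | 7.41% | +0.2% | 6.82% | −8% |
| 3 | 7.14% | −3.4% | 6.55% | −11% |

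At k = 1.5 the Kaplan-Meier error is +2.1%. On this schedule the overstatement shrinks, vanishes or reverses as mortality after onset rises. A naive competing-risk calculation is no better at k = 1 and worse at k = 2 and 3.

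**The case against.** The article is silent on deaths. That they are censored is inferred from the method, and the full protocol or analysis plan may contain a rule. This is fair, and the point should not be read as saying that the article prescribes censoring. But the estimator itself is stated, and in ordinary use it has no other place for a death without COPD.

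A reader might infer that the incidence will be overstated in any case. The documents do not support that. If the Abstract's year-four measurement is the only repeat spirometry, the sign depends on mortality after onset (Step 4).

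A reader might also infer that the group comparisons are invalid. They are not. The log-rank test, its trend version and the Cox model, with deaths censored, validly compare cause-specific hazards. Only the absolute curves, and risk contrasts read off them, are affected.

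It is also tempting to single out smokers. Secondary Measures lists "history and current status of tobacco, biomass fuel or occupational exposures" among the data collected, but the curve groups named are only quartiles or groups to be created. Age categories are explicit, so the oldest category is the safer example.

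Finally, the bias is small against sampling error in a single cell or site, and incidence is a secondary outcome. This stands. It limits the importance of the point but does not make Kaplan-Meier the right estimator of the share affected.

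**Conclusion.** The point holds in a limited form. If onset is observed and deaths are censored, one minus Kaplan-Meier exceeds the real cumulative incidence by about 1% at an annual death hazard of 0.005 and 10% at 0.05. That is 0.02 to about 1 percentage point over four years, and more where mortality is higher. In the example contrast, the risk ratio moves only from 1.96 to 1.89. All of this rests on assumed constant hazards. If spirometry is at baseline and year four only, neither the direction nor the size can be stated without an assumption about mortality after COPD onset; over the range tried at h = m = 0.02, the error runs from +4.0% to −3.4%. No figure in the article changes, and the primary outcomes are unaffected. This is a worthwhile refinement, not a serious flaw.

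**What to change.** State the spirometry schedule during follow-up and how deaths are handled in the incidence analysis. Then:

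- If onset is ascertained at annual visits, replace Kaplan-Meier with the Aalen-Johansen cumulative incidence, with death without COPD as a competing event.
- If spirometry is at baseline and year four only, use an interval-censored illness-death model and show results over a range of mortality after COPD onset. Do not count all deaths as COPD-free.
- In either case keep the log-rank tests and the Cox model, and label them as cause-specific hazard analyses, not as tests of the cumulative incidence curves.

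The cost is a few sentences and, under annual ascertainment, little extra analysis. Vital status is needed anyway to decide censoring. The illness-death model takes more work and brings an assumption that must be shown. The reported incidence will usually be slightly lower. The sample size does not change.
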